## ACRONYMS AND ABBREVIATIONS

|         |                                                  |
|---------|--------------------------------------------------|
| ANC     | Antenatal Care                                   |
| CHN     | Community Health Nurse                           |
| CHO     | Community Health Officer                         |
| CHPS    | Community-Based Health Planning and Services     |
| CHV     | Community Health Volunteer                       |
| CKI     | Community Key Informant                          |
| CoC     | Continuum of Care                                |
| DHMT    | District Health Management Team                  |
| EMBRACE | Ensure Mothers and Babies Regular Access to Care |
| FGD     | Focus Group Discussion                           |
| GHS     | Ghana Health Service                             |
| HDSS    | Health Demographic Surveillance System           |
| HIV     | Human Immunodeficiency Virus                     |
| HRC     | Health Research Center                           |
| JICA    | Japan International Cooperation Agency           |
| MDG     | Millennium Development Goals                     |
| MMR     | Maternal mortality ration                        |
| MNCH    | Maternal, neonatal and child health              |
| NMR     | Neonatal Mortality Ratio                         |
| PNC     | Postnatal Care                                   |

|       |                                     |
|-------|-------------------------------------|
| PMR   | Perinatal Mortality Ratio           |
| RHA   | Regional Health Administration      |
| SBA   | Skilled Birth Attendant             |
| SDHMT | Sub-district Health Management Team |
| TBA   | Traditional Birth Attendant         |
| ToT   | Training of Trainers                |
| U5MR  | Under-five mortality rate           |
| WHO   | World Health Organization           |

### **Funding and Resources**

This study is financed through a grant from JICA.

## **INTRODUCTION**

### **Background**

Maternal and neonatal morbidity and mortality continue to be prominent public health issues, particularly in developing countries. Maternal mortality remains extremely high, especially in Africa, despite a safe motherhood initiative launched about three decades ago. In the same vein, despite reductions in child mortality over the years, about 8 million children died worldwide in 2010. Of these deaths, 40% occurred during the neonatal period in the first month of life, and 98% of these neonatal deaths now take place in developing countries.

Millennium Development Goals (MDGs) 4 and 5 seek to reduce the under-five mortality rate (U5MR) by two-thirds and the maternal mortality ratio (MMR) by three-quarters, between 1990 and 2015. Progress, however, has been minimal and uneven across countries, especially in Sub-Saharan Africa. Unless an annual 7% decline is attained during the period between 2008 and 2015, it appears unrealistic for Sub-Saharan Africa to attain MDG 4.

In that context, the “Ensure Mothers and Babies Regular Access to Care” (EMBRACE) initiative was launched in 2010. This initiative was a strategy to step up Japan’s concerted efforts to help achieve the health-related MDGs in developing countries, particularly regarding maternal and child health. To extend the benefits of the EMBRACE initiative and evidence-based practice in health policy, the Ghana EMBRACE implementation research project was launched in 2012. Following the results of the formative research, a package of interventions was developed and will be implemented in three Health and

Demographic Surveillance System (HDSS) sites in Ghana.

***Maternal, neonatal and child health in Ghana***

Under-five mortality decline has been very slow in Ghana. According to the Ghana Demographic and Health Survey (GDHS) 2008, Ghana's neonatal mortality ratio(NMR) was estimated at 30 deaths per 1,000 live births. This represents only a slight decline from the 35 deaths per 1,000 live births reported in the preceding survey in 2003. Moreover, mortality levels in rural areas are consistently higher than those in urban areas. NMRs for urban and rural settings were 30 and 34 per 1,000 live births, respectively.

In the same vein, Ghana's MMR remains remarkably high despite the efforts made by the Government of Ghana and its international development partners. Recent data show that the MMR for Ghana was 350 deaths per 100,000 live births in 2008. Based on sibling history with verbal autopsy, the Ghana Maternal Health Survey (GMHS) also estimated the pregnancy-related mortality ratio (PRMR) at 580 deaths per 100,000 live births when counting the household deaths in 2007. The major single cause of maternal death was hemorrhage, which yet remains still remains a leading cause (22.9%), followed by abortion (12.3%) and hypertensive disorders of pregnancy (10.4%),In Ghana, the percentage of births attended by a skilled health service provider has registered a similarly slow progress, increasing from 40% in 1988 to only 59% in 2008.

Many of these deaths are preventable, if only appropriate measures could be put into place in advance. In order to support countries in Sub-Saharan Africa to move towards the attainment of the MDGs, the African Regional Reproductive Health Taskforce meeting was held in Dakar in 2003. Consequently, the MDG Acceleration Framework was developed by the Ministry of Health (MoH) and Ghana Health Service (GHS) in

collaboration with development partners in Ghana. The Framework aims to redouble efforts to overcome bottlenecks in implementing interventions that have been proven effective in reducing MMR in Ghana.

### ***Continuum of care in maternal, neonatal and child health***

The continuum of care (CoC) in maternal, neonatal and child health (MNCH) has been played up as a strength in improving the health of mother and child. The WHO and other leading global health agencies in particular, have been advocating over the last decade, the potential power of the CoC in the context of MNCH. The concept of CoC has emerged as a new paradigm to address maternal, newborn and child mortality and is crucial to battling all of these forms of mortality.

However, the definition of CoC has not been clearly established yet, though several attempts have been made. The term itself is well known in the health systems in the context of palliative care nursing. In the public health field, the concept of CoC has been used in care of people living with HIV/AIDS, to link diagnosis, initiation of care, retention in therapy, and maintenance of a low viral load. With regards to the area of MNCH, the broad consensus on CoC incorporates integrated service delivery from pre-pregnancy to postnatal care, at home, community, and in health facilities. It is often explained by the dimensions of time and space: In the time dimension, CoC spans the period from pre-pregnancy to childhood for women and children. In the space dimension, meanwhile, it reaches from the home, to the community level, and through health facilities.

The components of CoC forming the intervention package to be implemented EMBRACE study are as follows:

- (1) At least four antenatal care (ANC) visits with MNCH skilled health service providers at the health facility, within the community, or at home;
- (2) Delivery assisted by skilled birth attendants (SBAs);
- (3) A minimum of three postnatal care (PNC) visits with MNCH health service providers at a health facility, in the community, or at home within 48 hours, on the seventh day, and at the end of six weeks postpartum consecutively.

The CoC in MNCH provides a framework whereby several evidence-based interventions can be combined and delivered in packages. Interventions included in such packages can be selected out of more than 190 separate interventions, and they can be delivered using this mode of integrated service delivery. As maternal and newborn health are closely related, the main focus of the CoC was once on maximizing maternal and newborn survival through promoting regular access to reproductive and maternal health care for women, particularly during pregnancy and childbirth. However, the CoC also can be effective to improve care and to reduce morbidity, too. An effective intervention is required to cover the cracks along with the time and space dimensions of the CoC by strengthening the linkages between various levels of health systems and between service delivery packages.

### ***Implementation research***

To make health service interventions more effective, it is necessary to understand how interventions work in “real world” setting. Implementation research has a role in solving such implementation problems, taking into account the social, demographic, cultural, and economic environment; the epidemiological conditions; and the institutional setting. Both qualitative and quantitative research methods can be used in implementation research,

and several approaches have been developed to deal with the associated questions: pragmatic trials, effectiveness implementation hybrid trials, quality improvement studies, participatory action research, and mixed methods. These approaches may be applied according to the circumstances prevailing in the intervention areas, with due consideration given to their limitations.

### **Rationale for Study**

According to currently available evidence, Ghana is not on track to achieve MDGs 4 and 5. Despite increases in ANC attendance at the health facilities, and in the number of deliveries attended by skilled health service providers, the needed declines in neonatal and maternal mortality have not been seen. In addition, according to our formative research in Ghana, the CoC completion rate was only 10% among women in Ghana. In particular, an abrupt drop was identified in the care uptake rate at the within-48-hours-postpartum PNC stage, underlining a prominent crack in the CoC time dimension that requires urgent action for improvement.

Ghana has multiple localities, characterized by the unique environmental qualities of each area. Maternal and neonatal deaths are a function of a complex interaction of economic, financial, social, cultural and clinical factors. The diversity of local characteristics demands flexibility in health service provision. As such, it is especially important to conduct the implementation trials in Ghana in the different local contexts.

### **Hypothesis**

Implementation of an integrated package of CoC intervention improves the following

MNCH intervention and implementation impact outcomes within one year among the target population in rural Ghana.

## **Objectives**

The study aims to improve MNCH status by strengthening the MNCH CoC in rural Ghana. Specific objectives are proposed for intervention and implementation phases. In the public health context, a health program is planned toward achieving population health goals or around objectives designed to improve quality of life. An intervention is one component of such a program and a method of initiating a process to attain such goals and objectives. Typically, a program consists of multiple interventions which are planned based on the people's needs and in light of the desired outcome and its impact. However, to integrate the study findings and products into routine and sustainable use, it is necessary to adopt an appropriate concept and theory on which to base the interventions. An implementation process thus comprises the effort of applying the theoretical framework of an intervention to the real circumstances on the ground.

### ***Intervention objectives***

- To evaluate the impact of interventions on the CoC completion rate.
- To evaluate the impact of an improved CoC completion rate on health outcomes among mothers and infants.

### ***Implementation objective***

- To examine the feasibility of the planned CoC interventions in rural Ghana.

## **METHODS**

### **Study Setting**

The study will be carried out at three different Health and Demographic Surveillance System (HDSS) sites of the GHS in Ghana: Dodowa (Greater Accra region), Kintampo (Brong-Ahafo region), and Navrongo (Upper East region). See figure 1. These three sites were selected based on the high reliability of HDSS data for evaluating the study's impact. The feasibility of implementation will be evaluated in different contexts. The HDSS involves a semi-annual recording of vital demographic events, including pregnancies, births, deaths, and migration, occurring among residents of all households in the HDSS area. Other data are also collected and updated regularly, such as household characteristics, morbidity, and vaccination uptake.

The Dodowa HDSS site registered a surveillance population of approximately 115,000 as of 2011. The site is located only about 40 kilometers away from Accra. Consequently, pregnant women of this site often prefer to access health facilities in Accra to give birth. Delivery of services is, however, generally challenging due to the large land size, covering about 40.5% of the Greater Accra Region. Most of the communities are scattered, with small population sizes.

In Kintampo, the surveillance population numbered approximately 200,000 in 2011. The Kintampo HDSS site is a multi-ethnic area, and farming is the most important economic activity. Apart from the central area, few villages have electricity and most are reached by dirt roads. Access to health facilities is particularly challenging in Kintampo. One-third of pregnant women did not deliver in health facilities, according to our situation analysis.

In Navrongo, the surveillance population numbered approximately 153,000 in 2011. Navrongo is the first area where the Community-based Health Planning and Services (CHPS) program was launched in Ghana. In that context, Community Health Officers (CHOs) contribute to improving the health status of the rural community. Almost 90% of women delivered at health facilities and received PNC within 48 hours of giving birth, according to our situation analysis.

[figure not shown]

**Figure 1** Map of Health Research Centers

## Overview of Study Design

### *Trial design*

This study has been designed as an effectiveness-implementation hybrid trial, testing the effectiveness of the intervention as well as the feasibility of its implementation strategy. Under this study design, the effectiveness will be assessed for both an intervention package and its implementation process by using cluster-randomized allocation to divide participants into intervention and control arms. The study would be conducted in three stages, namely: the baseline, implementation and evaluation phases. Feasibility of the trials will be also be evaluated through monitoring on-going trials by

district health management team (DHMT)/sub-district health management team (SDHMT) supervisors. Supervisors such as the public health nurse, the disease control officer, for e.g. from the DHMT and SDHMT already have monitoring responsibilities, which will be further enforced by the refresher training as part of the intervention.

### ***Study schedule***

- (i) Baseline survey: 1 July 2014 to 31 July 2014
- (ii) Intervention: 1 October 2014 to 31 December 2015**
- (iii) Evaluation survey: 1 September 2015 to 31 October 2015
- (iv) Analysis/writing: From November 2015

### **Outcome measures**

Implementation of an integrated CoC intervention package is expected to improve the following MNCH intervention and implementation impact outcomes within one year within the target population in rural Ghana:

### ***Intervention impact outcomes***

The primary outcome of the intervention is 1) CoC completion rate of mothers and infants. Secondly, outcomes such as 2) the PNC rate within 48 hours postpartum, 3) the rate of complications requiring hospitalization of mothers and their infants for more than 24 hours, and 4) the perinatal mortality ratio (PMR) will be measured. All the data will be compared between intervention and control arms.

### ***Implementation impact outcomes***

The implementation impact outcomes are 1) acceptability of CoC card utilization and 2) feasibility of improved PNC rates within 48 hours postpartum by mothers' retention at the health facility or by home visits. These outcomes are to be compared before and after the intervention.

### **Study Population**

Pregnant women will be recruited as participants of the study from the areas of Dodowa, Kintampo and Navrongo HDSS. Eligibility criteria will be as follows.

(i) Participants of the baseline survey:

Study population would be females who got pregnant in the target HDSS sites. The inclusion criteria are those who gave birth within the two years preceding the baseline survey, including live-births and still-births. The exclusion criteria will be those who have infants younger than six weeks of age at the beginning of the data collection.

(ii) Participants of the intervention and evaluation survey:

The study population would be females who got pregnant in the target HDSS sites. The inclusion criteria will be those who are between 16 weeks gestation and six weeks postpartum during the intervention period of A-1, B-1 and B-2 **(1st October 2014 to 31st December 2015)** including live-births and still-births. The exclusion criteria will be those who have infants younger than six weeks of age at the beginning of the data collection. From preliminary information gathered from the participating three HDSS sites, during the intervention period, about **27,500** mothers are expected to experience pregnancy, delivery, or the postnatal period in the study sites, and these will form the target population in this study. **An**

estimated total of 10,000 mothers are expected to be fully followed up from their first ANC visit to their PNC visit at six weeks post-partum (approximately 5,000 intervention and 5,000 control arms), which accounts for 36 % of all target mothers. The remaining 64% will be also followed up as they will partially receive the intervention; those who registered at their first ANC before the start of intervention, and those whose third PNC period occurs after the intervention period. See table below.

| Year                 | 2014          |   |   |   |   |   |   |                |    |    |   |   | 2015 |   |   |               |   |   |   |    |    |    |  |  |
|----------------------|---------------|---|---|---|---|---|---|----------------|----|----|---|---|------|---|---|---------------|---|---|---|----|----|----|--|--|
| Month                | 3             | 4 | 5 | 6 | 7 | 8 | 9 | 10             | 11 | 12 | 1 | 2 | 3    | 4 | 5 | 6             | 7 | 8 | 9 | 10 | 11 | 12 |  |  |
| 1: Partial follow-up | 8,750 mothers |   |   |   |   |   |   |                |    |    |   |   |      |   |   |               |   |   |   |    |    |    |  |  |
| 2: Full follow-up    |               |   |   |   |   |   |   | 10,000 mothers |    |    |   |   |      |   |   |               |   |   |   |    |    |    |  |  |
| 3: Partial follow up |               |   |   |   |   |   |   |                |    |    |   |   |      |   |   | 8,750 mothers |   |   |   |    |    |    |  |  |

Figure 2 Three sub-groups of the target mothers categorized by month of conception

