## **Impact Evaluation**

To evaluate the impact of the intervention package, the baseline and evaluation surveys will be conducted in three HDSS sites. The period of the baseline survey will be from July to August 2014. **The intervention period will run from October 2014 to December 2015. Period of the last three months (October to December 2015) will be added to mitigate the decline in the service quality due to the abrupt intervention cessation. The evaluation survey period will be from October to November 2015, and the survey's target will not include the mothers who would newly enter this period, thus the survey results would not be influenced by the addition of the period.**

Individual mother- and infant-level data will be collected regarding their CoC MNCH completion rates, complication rates, within-48-hours-postpartum PNC rates, mortality and adverse outcomes. In the baseline survey, data will be collected through household surveys of mothers who delivered within the two years preceding the survey. In the evaluation survey, mothers will be included if they have received any aspect of MNCH care, even in part, during the intervention period. However, for data from those who cannot be fully followed up during the intervention period, analyses will be performed according to the care stages they received during the intervention period. This may be analyzed separately from mothers who have passed the period from the first ANC session to the PNC at six weeks during the intervention period. Individual mother- and infant-level data will also be obtained from the HDSS data set regarding pregnancy outcomes

and morbidity.

To evaluate the impact of the implementation, a set of data and supporting information will be collected during the supervision by the DHMT/SDHMT. **This includes the status of CoC card distribution and actual users, as well as uptake of PNC within 48 hours postpartum, either by retention of mothers at the facilities or by home visits. In addition, qualitative data of women and health workers will be collected during the monitoring by the researchers. Those include transcript data of interview, audio-visual data (photographic and motion data) which will be collected through the in-depth interviews. Target of in-depth interview will be women and health workers who will be involved in the intervention or control arm.**

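### The 10,000 fully followed mothers are counted to 31 December 2015, but the evaluation survey closes earlier and can observe the whole pathway in only about 5,100 to 6,400 of them

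*Protocol*

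**What the plan says.** All places are in the protocol.

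- **Study Population (ii)** sets the period as 1 October 2014 to 31 December 2015 and puts the target population at 27,500. It then says that "10,000 mothers are expected to be fully followed up from their first ANC visit to their PNC visit at six weeks post-partum". These are divided equally between the two arms, 5,000 in each, and their share of the 27,500 is given as 36%. The same section excludes mothers whose infants are under six weeks old when data collection begins.
- **Figure 2** splits the 27,500 into 8,750, 10,000 and 8,750. The three groups begin in the March 2014, October 2014 and June 2015 columns. The caption reads "Figure 2 Three sub-groups of the target mothers categorized by month of conception".
- **Study schedule**: "Evaluation survey: 1 September 2015 to 31 October 2015".
- **Impact Evaluation**: "The evaluation survey period will be from October to November 2015". It explains that October to December 2015 was added to soften the end of the intervention, and that the survey's "target will not include the mothers who would newly enter this period".
- **Outcome measures** makes CoC completion the primary outcome. By the definition in the Background, completion runs to the postnatal visit at six weeks.

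**The concern.** The count of fully followed mothers runs to the end of December 2015. Both versions of the survey window close before then, and they disagree with each other. A mother who reaches six weeks postpartum after the survey cannot report that visit in it. Impact Evaluation names no other source for completion: it takes pregnancy outcomes and morbidity from the surveillance (HDSS) data set, and card use and 48-hour postnatal care from supervision. The fully followed mothers are the only group whose whole pathway falls under the intervention, so a reader will take 10,000 as the number behind the cleanest estimate of the primary outcome.

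**Working it through.** **1. Reproduce the stated counts.** The Figure 2 groups start in March 2014, October 2014 and June 2015, and the grid ends in December 2015. That gives 7 + 8 + 7 = 22 monthly cohorts.

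- 27,500 / 22 = 1,250 per month; 8,750 / 7 and 10,000 / 8 give the same rate.
- 8 × 1,250 = 10,000, and 10,000 / 27,500 = 36.4%. The stated figures reproduce.

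**2. Find the period they imply.** From 16 weeks' gestation to six weeks postpartum is 24 + 6 = 30 weeks at a 40-week term. Entry on 31 May 2015, the end of the eighth cohort, plus 30 weeks gives 27 December 2015. By exact days to 31 December, the latest entry is 4 June 2015: 246 days × 41.07 per day (1,250 × 12 / 365.25) = 10,103. So 10,000 needs follow-up to the end of December.

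**3. Apply the survey rule.** Latest entry = survey start − 6 weeks (infant age) − 24 weeks (16 weeks to term). Count = days from 1 October 2014 to latest entry × 41.07.

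| Survey start | Latest birth | Latest entry | Days | Mothers | Per arm | Share of 27,500 |
|---|---|---|---|---|---|---|
| 1 Sep 2015 | 21 Jul 2015 | 3 Feb 2015 | 125 | 5,133 | 2,567 | 18.7% |
| 1 Oct 2015 | 20 Aug 2015 | 5 Mar 2015 | 155 | 6,366 | 3,183 | 23.1% |

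Against 10,000, that is 49% and 36% fewer.

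**4. Vary the assumptions.** The gestation at first antenatal visit is not given, so 12 to 24 weeks is assumed as a range. The last two rows apply the six-week rule up to the last survey day, which is not what the text says.

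| Rule | 12 weeks | 16 weeks | 20 weeks | 24 weeks |
|---|---|---|---|---|
| Start 1 Sep | 3,984 | 5,133 | 6,283 | 7,433 |
| Start 1 Oct | 5,216 | 6,366 | 7,515 | 8,665 |
| Rolling to 31 Oct | 6,448 | 7,598 | 8,747 | 9,897 |
| Rolling to 30 Nov | 7,680 | 8,830 | 9,979 | 11,129 |

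With the rule as written, every value is below 10,000. About 10,000 is reached only by combining a rolling rule with a late first visit: about 20 weeks to 30 November, or 24 weeks to 31 October.

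**5. Size of the precision loss.** For equal clusters, the standard error is proportional to √[(1 + (m − 1)ρ) / m], where m is mothers per cluster and ρ the intracluster correlation (ICC). With 32 clusters, m falls from 10,000 / 32 = 312.5 to 5,133 / 32 = 160.4 or 6,366 / 32 = 198.9. The protocol gives no ICC, so two values are assumed.

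- ρ = 0.05: variance terms 0.0530 against 0.0559 and 0.0548; standard error up 2.7% and 1.6%.
- ρ = 0.01: 0.01317 against 0.01617 and 0.01498; standard error up 10.8% and 6.7%.

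**6. Check the caption.** Conception on 31 May 2015 plus 38 weeks gives birth on 21 February 2016, and six weeks postpartum on 3 April 2016, after the intervention ends. Read literally as conception month, only about 6,080 mothers would complete by 31 December 2015. The counts fit month of reaching 16 weeks.

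**7. The 27,500.** Its third group includes entrants in October to December 2015, 3 × 1,250 = 3,750, whom Impact Evaluation leaves out of the survey.

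**The case against.** The strongest reply is that 10,000 is an expected number of mothers fully exposed by 31 December, nowhere called the survey's evaluable sample, and that for that period the arithmetic is right. This stands. A reader might infer that the figure is a calculation error or can never be reached; step 1 shows otherwise. The defect is a mismatch between the counting period and the observation period.

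Other inferences that the protocol does not support:

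- **That leaving new October to December entrants out of the survey shrinks the 10,000.** On the 16-week reading those mothers entered from October 2014 to May 2015, so that sentence removes none of them. The fall comes from the survey dates and the six-week rule.
- **That a total surveyable number can be fixed by counting delivered women.** Impact Evaluation admits mothers who received only part of the care, and the exclusion does not touch women still pregnant.
- **That complications and perinatal mortality suffer most.** Partially followed mothers are analysed by care stage, and HDSS data also supply pregnancy outcomes and morbidity.
- **That the caption would misclassify mothers in analysis.** Impact Evaluation separates full from partial follow-up by the span from first antenatal visit to six-week visit, not by conception month.
- **That a large loss of power follows.** No power, effect size or ICC is stated, and step 5 shows a modest effect on precision.

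It is also fair to say that 5,100 and 6,400 are not exact, because they depend on an assumed gestation at first visit. They need the range in step 4 beside them.

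**Conclusion.** The point holds as a mismatch that is wrong as written. The 10,000 (5,000 per arm, 36%) describes exposure to 31 December 2015. The survey that collects the primary outcome has two conflicting windows, both ending earlier. Under the six-week exclusion as written it can observe the complete pathway in about 5,100 (1 September) or 6,400 (1 October) mothers, within about 4,000 to 8,700 for a first visit at 12 to 24 weeks. A six-week rule running to the last survey day, with 16-week entry, would give 7,600 to 8,830. All of this assumes even entry of 1,250 per month and a 40-week term. The consequence is an overstated head count for observable CoC completion. The cost in precision is smaller: about 2–3% in standard error at an assumed ICC of 0.05 and 7–11% at 0.01.

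**What to change.** 1. Give one evaluation-survey window, identical in Study schedule and Impact Evaluation.
2. In Study Population, say that 10,000 is exposure to 31 December 2015. Add the number with observable CoC completion for the chosen window, with its assumptions (entry rate, term, gestation at first visit, day on which the six-week rule applies) and its range. Alternatively, set the window so that the stated 10,000 can be observed; with the rule applied on the first day, that means a start no earlier than about 27 December 2015.
3. Say that 27,500 is the target population and not the number to be surveyed.
4. Change the Figure 2 caption to month of reaching 16 weeks' gestation.

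Restating costs only protocol wording and a less favourable stated size; no further participants are needed. Moving the survey costs time: analysis is scheduled from November 2015 and community feedback of results for January 2016, and both would have to move.
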